# Chatbot-Led Support Combined With Counselor-Led Support on Smoking Cessation in China: Protocol for a Pilot Randomized Controlled Trial

**DOI:** 10.2196/58636

**Published:** 2024-09-23

**Keywords:** chatbot, smoking cessation, mHealth, mobile phone, campus, China

## Abstract

**Background:**

China has a large population of smokers, with half of them dependent on tobacco and in need of cessation assistance, indicating the need for mobile health (mHealth) to provide cessation support.

**Objective:**

The study aims to assess the feasibility and preliminary effectiveness of combining chatbot-led support with counselor-led support for smoking cessation among community smokers in China.

**Methods:**

This is a 2-arm, parallel, assessor-blinded, pilot randomized controlled trial nested in a smoke-free campus campaign in Zhuhai, China. All participants will receive brief face-to-face cessation advice and group cessation support led by a chatbot embedded in WeChat. In addition, participants in the intervention group will receive personalized WeChat-based counseling from trained counselors. Follow-up will occur at 1, 3, and 6 months after treatment initiation. The primary smoking outcome is bioverified abstinence (exhaled carbon monoxide <4 parts per million or salivary cotinine <30 ng/mL) at 6 months. Secondary outcomes include self-reported 7-day point prevalence of abstinence, smoking reduction rate, and quit attempts. Feasibility outcomes include eligibility rate, consent rate, intervention engagement, and retention rate. An intention-to-treat approach and regression models will be used for primary analyses.

**Results:**

Participant recruitment began in March 2023, and the intervention began in April 2023. The data collection was completed in June 2024. The results of the study will be published in peer-reviewed journals and presented at international conferences.

**Conclusions:**

This study will provide novel insights into the feasibility and preliminary effectiveness of a chatbot-led intervention for smoking cessation in China. The findings of this study will inform the development and optimization of mHealth interventions for smoking cessation in China and other low- and middle-income countries.

**Trial Registration:**

ClinicalTrials.gov NCT05777005; https://clinicaltrials.gov/study/NCT05777005

**International Registered Report Identifier (IRRID):**

DERR1-10.2196/58636

## Introduction

China has the world’s largest population of tobacco users, with more than 300 million current smokers [1]. Approximately half of these smokers are dependent on tobacco and require cessation assistance [2]. Traditional smoking cessation programs, including pharmacotherapy and behavioral counseling [3], have shown efficacy but face challenges such as limited accessibility and high costs in China [4,5], highlighting the need for innovative and scalable interventions.

Mobile health (mHealth) interventions have proven effective in increasing smoking abstinence [6] by enhancing perceived behavioral and psychosocial support for quitting [7]. However, most current mHealth studies rely on fixed-schedule text messages [8-10], which may limit personalization and engagement [11]. Mobile instant messaging (IM) apps (eg, WeChat or WhatsApp) offer more tailored and interactive behavioral and psychosocial support between smokers and smoking cessation counselors. Our previous trials in China found that personalized cessation support via IM, combined with a brief intervention, significantly increased both smoking cessation service utilization and smoking cessation rates [12]. Our pilot trial indicated the feasibility and preliminary efficacy of integrating personalized counselor support via IM with pharmacotherapy [13]. Other trials in China have corroborated these findings, showing the efficacy of IM-based cessation support in increasing abstinence rates [14-16].

Nonetheless, high attrition rates remain a challenge in mHealth interventions. A meta-analysis found a 40%-50% dropout rate in mHealth interventions [17], and our studies observed suboptimal adherence to real-time counselor support, with only about 17% of participants engaging in real-time communication with counselors [12,18]. This limited engagement may be attributed to counselors being available only during working hours, thereby reducing the timeliness and convenience of the support.

Chatbots, automated conversational agents that leverage artificial intelligence and natural language processing to simulate human-like conversations [19], offer a novel opportunity for delivering personalized and interactive cessation support at scale. Unlike human counselor support, chatbots are available 24/7, providing personalized and instant feedback and facilitating psychosocial support [20]. Prior research on chatbot interventions for smoking cessation has shown promise, particularly in enhancing user engagement and adherence to cessation programs [21]. However, our previous trial, which integrated chatbot support with pharmacotherapy and real-time counselor support, did not significantly improve abstinence rates compared with general health messages [22]. The evidence of the effectiveness of chatbots for smoking cessation is not conclusive, with generally small effect sizes [20]. More research is needed on chatbot interventions to determine their efficacy in smoking cessation, particularly in combination with other support modalities in real-world settings.

This study aims to evaluate the integration of chatbot-led support with counselor-led support in promoting smoking cessation among Chinese smokers. The specific objectives of the study are to (1) assess the feasibility of a chatbot-led support intervention for smokers in China, and (2) compare the preliminary efficacy of chatbot-led support combined with counselor-led support versus chatbot-led support alone.

## Methods

### Study Design

This is a 2-arm, assessor-blinded, pilot randomized controlled trial nested in a smoke-free campus campaign in Zhuhai, China. The campaign is jointly organized by the Youth League and the Staff Union of the Beijing Normal University, Zhuhai, and aims to promote smoking cessation and health education among students and staff [23]. The campaign includes a series of activities, including a “Health for the Future” Smoke-free Promotion Competition that allows students to design publicity materials, a “Smoke-free Ambassador” Competition in which smoke-free volunteers can receive training and recognition, and a “Smoke-free Campus” Smoking Cessation Contest that motivates smokers to quit. The design adheres to the CONSORT (Consolidated Standards of Reporting Trials) statement recommendations (Figure 1) [24].

**Figure 1 figure1:**
[figure not shown]
CONSORT (Consolidated Standards of Reporting Trials) flow diagram.

### Lay Counselor Recruitment and Eligibility

Similar to our previous trials [25-27], university students will be recruited and trained as lay counselors to provide brief cessation advice to community smokers. Recruitment will be advertised through the website and WeChat official account of the university’s volunteer organizations. Eligibility criteria for the lay counselors are as follows: (1) current university students aged 18 years and older; (2) the time and commitment to attend the training sessions and pass the posttraining assessments; and (3) the ability to provide informed consent.

### Participant Recruitment and Eligibility

Web-based promotional strategies will be used to recruit participants through the social media websites of student associations, posters and flyers, and referrals. On-site recruitment activities will be conducted in high-traffic areas on campuses, such as the campus canteen and dormitories. Trained counselors will proactively approach smokers using the “foot-in-the-door” approach [28]. This approach has been extensively used in our previous community trials [25-27] and involves engaging smokers, explaining the study, and inviting them to join the study. The counselors will provide detailed information about the study and the benefits of quitting and the incentives offered. Participants will receive a cash incentive of RMB 100 (approximately US $14) for passing the biochemical validation at 3 and 6 months.

Participant eligibility criteria are intended to be inclusive to maximize generalizability and reach. Eligibility criteria include age of 18 years and older; daily smokers, defined as those smoking ≥1 cigarette per day in the past 3 months; exhaling carbon monoxide ≥4 ppm, indicating active smoking; having a smartphone with WeChat installed; and being motivated to quit smoking or reduce smoking, as assessed using the Transtheoretical Model. Smokers with physical or cognitive communication difficulties or those in other smoking cessation programs will be excluded. All eligible smokers willing to participate will sign a written informed consent form.

Smokers will be informed that the intervention involves a baseline assessment of their exhaled carbon monoxide level, brief questions on past smoking behaviors (baseline questionnaire), and further telephone interviews (follow‐up questionnaires at 1, 2, 3, and 6 months).

### Randomization and Blinding

Participants will be individually randomized in a 1:1 ratio to the intervention or control group. The allocation of participants to the intervention and control groups will be conducted using a computer-generated randomization list. To ensure balance, a randomized blocking schema with block sizes of 2, 4, or 6 will be implemented. Blinding is not possible for the interventionists and participants due to the nature of the intervention. Outcome assessors and statistical analysts will remain masked until the predefined analyses are completed.

### Sample Size

There is no fixed rule for calculating sample size for a pilot study [29]. Prior research on the estimation of sample sizes for pilot studies indicates that a sample of 50 participants per group should be sufficient to achieve 80% power to detect differences between groups [30] on the assumption of a 5% significance level and a 10% attrition rate. Therefore, a total of 150 participants will be recruited for this study.

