This study has several limitations that should be acknowledged. First, the sample size in this study can assess only the preliminary effectiveness of the intervention. Thus, all results should be treated as preliminary, and conclusive results await a fully powered trial. Second, the absence of a control group without a chatbot-led intervention limits the comparison of the intervention outcomes, potentially confounding the interpretation of the intervention’s true efficacy. Third, this study will assess only the short-term and midterm effectiveness of the intervention (ie, 3 months and 6 months after treatment initiation), which precludes the evaluation of long-term smoking abstinence (eg, 12 months) and relapse rates. Finally, the study is conducted in a campus setting, where participants are primarily students who are well educated and may be more responsive to mHealth interventions, limiting the generalizability of the findings to other populations.

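### The 80% power claim names no outcome or difference, and 50 per group does not lead to a total of 150 in a two-arm trial

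*Protocol article*

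**What the plan says.** The Sample Size section of the protocol article first notes that pilot studies have no fixed sample-size rule. It then cites prior research that "a sample of 50 participants per group should be sufficient to achieve 80% power to detect differences between groups", "on the assumption of a 5% significance level and a 10% attrition rate". The next sentence is: "Therefore, a total of 150 participants will be recruited for this study".

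The design is stated elsewhere. Study Design: "This is a 2-arm, assessor-blinded, pilot randomized controlled trial". Randomization and Blinding: "Participants will be individually randomized in a 1:1 ratio to the intervention or control group". A total of 150 therefore means 75 per arm. Under Outcomes, the primary smoking outcome is binary: biochemically validated 7-day point prevalence abstinence at 6 months. The Abstract specifies an intention-to-treat approach for the primary analyses.

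The limitations paragraph of the Discussion says that the numbers allow only a preliminary look at effectiveness and that "conclusive results await a fully powered trial".

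**The concern.** Power is a property of a test against a stated difference. The section gives a significance level and an attrition rate, but the target is only "to detect differences between groups". It gives no outcome, control or intervention rate, or sidedness, and the rest of the article supplies no abstinence rate. The 80% therefore has no checkable meaning for 6-month validated abstinence.

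The total is presented as a consequence of the per-group figure, yet the article's own design does not turn one into the other.

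What is at stake is how the result is read. Someone who takes the Sample Size section at its word could describe a non-significant abstinence comparison as coming from a trial with 80% power. The size of the trial and its estimates are not affected.

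**Working it through.** **Inputs from the article:** 50 per group, 80% power, 5% significance, 10% attrition and a total of 150 (Sample Size); 2 arms (Study Design); 1:1 allocation (Randomization and Blinding); binary primary outcome at 6 months (Outcomes). **Not given:** abstinence rates, sidedness, and whether the 50 is before or after attrition.

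**Step 1: can 150 be reproduced?**

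- The 50 already covers attrition: 2 x 50 = 100.
- Attrition still to be added: 50 / (1 - 0.10) = 55.6, rounded up to 56; 2 x 56 = 112.
- Inflating by multiplication instead: 2 x 50 x 1.10 = 110.
- Attrition that would turn 100 into 150: 1 - 100/150 = 33%, not 10%.

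No variant gives 150. The planned 75 per arm exceeds both 50 and 56, so the surplus is 150 - 112 = 38 to 150 - 100 = 50 participants.

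**Step 2: can the 80% be reproduced?** Not without a difference. The question can be inverted: what difference would each sample size detect with 80% power? Pooled-variance two-proportion test, two-sided 5%, n per arm, with p̄ = (p1 + p2)/2:

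power = Φ{ [ (p2 - p1)√n - 1.96 √(2p̄(1 - p̄)) ] / √( p1(1 - p1) + p2(1 - p2) ) }

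Example, p1 = 0.10, p2 = 0.20, n = 75: the numerator is 0.10 x 8.660 - 1.96 x √0.255 = 0.866 - 0.990 = -0.124; the denominator is √(0.09 + 0.16) = 0.5; Φ(-0.247) = 0.402.

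The 95% CI half-width for the risk difference at 10% versus 20% is 1.96 √(0.25/n).

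All rates below are assumptions. The three control-rate columns give the intervention rate needed for 80% power.

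| n per arm | control 5% | control 10% | control 20% | power, 10% vs 20% | CI half-width, 10% vs 20% |
|---|---|---|---|---|---|
| 50 (cited rule) | 24.7% | 32.7% | 46.0% | 28.6% | 13.9 points |
| 67 (75 less 10%) | 21.2% | 29.0% | 42.2% | 36.6% | 12.0 points |
| 75 (all randomized) | 20.0% | 27.8% | 40.9% | 40.2% | 11.3 points |

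The 75 row fits the intention-to-treat approach in the Abstract. The 67 row applies if only those retained after 10% attrition are analyzed (75 x 0.9 = 67.5).

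**Step 3: sensitivity.** A one-sided 5% test raises power for 10% versus 20% to 40.2% at 50 per arm and 52.8% at 75. A larger assumed gain, 10% versus 30%, has two-sided power of 71.1% at 50 per arm and 87.2% at 75. Whether 80% is reached depends entirely on the difference assumed, and the article does not state one.

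**The case against.** The strongest reply is that a pilot needs no power calculation, that the section says there is no fixed rule, and that preliminary effectiveness is the declared aim throughout. This stands as far as it goes: omitting a calculation would have been acceptable. The article instead asserts one and draws its total from it.

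The 80% is also attributed to a cited source that may define an effect size. That is fair. It cannot be said that no effect lies behind the figure, only that the article neither states one nor ties it to its primary outcome.

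Several stronger readings are tempting and not supported:

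- *The trial is too small for its own inputs.* It is not; 75 per arm exceeds what they require.
- *A third arm was dropped.* 3 x 50 does equal 150, but nothing in the article points to a third group, and with 10% attrition three groups would need 3 x 56 = 168.
- *The Discussion contradicts the power figure.* It quotes no power. The two statements are in tension in meaning, not in numbers, and the warning that results are preliminary partly protects a reader of the whole article.
- *Power is low for every plausible gain.* The article gives no abstinence rates, and at 75 per arm a rise from 10% to 30% would have 87% power. Whether such a gain is plausible cannot be settled from the document.

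**Conclusion.** The point holds in two parts. First, the 80% power is tied to no stated outcome or difference and cannot be verified for the primary outcome. Second, 150 does not follow from 50 per group and 10% attrition in a two-arm 1:1 trial, where those inputs give 100 or 112. The second part rests only on the article's own figures. The tension with the Discussion supports the point but is not needed for it.

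On size, the 80% would be true at 75 per arm only for increases of about 15 to 21 percentage points over control rates of 5% to 20%, and a rise from 10% to 20% would have about 40% power. These figures assume the control rates shown, a two-sided 5% test and all randomized participants analyzed. The fault is in the stated justification, and no change to the number of participants follows from it.

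**What to change.** Keep 150. Delete the 80% power claim and the word that presents 150 as its consequence. Justify 150 by feasibility and precision, along these lines:

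> A total of 150 participants (75 per arm) will be recruited; this number was chosen on grounds of feasibility and precision. Abstinence rates are not known in advance, and the following are assumptions. With all 75 per arm analyzed by intention to treat and a two-sided 5% test, 80% power would require 6-month validated abstinence of about 20% versus 5%, 28% versus 10%, or 41% versus 20%. Power for 20% versus 10% is about 40%, with a 95% confidence interval for the risk difference of about ±11 percentage points. If 67 per arm are analyzed after 10% attrition, the required rates are about 21%, 29% and 42%, power is about 37% and the interval about ±12 points.

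The sponsor should add the actual practical reason for choosing 150. In the results paper, report the preliminary efficacy comparison as an estimate with its 95% confidence interval, and do not describe a non-significant result as coming from a trial with 80% power. The objective of comparing preliminary efficacy can stay.

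The cost is one paragraph and a less favorable power statement. No participants are added. The Abstract reports that data collection was completed in June 2024, so the correction now bears on reporting.

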### Interventionist Training and Supervision

All lay counselors will be required to attend a workshop before participant recruitment. The training covers three key domains: (1) an overview of the intervention content including the 5A/5R advice, chat-led support and counselor-led support, with a demonstration of recruitment strategies such as the foot-in-the-door approach, and the use of exhaled carbon monoxide tests; (2) detailed knowledge of the harms of smoking and the benefits of quitting; and (3) smoking cessation methods and counseling techniques. A pre- and posttest survey will evaluate changes in counselors’ knowledge, attitudes, and practices related to smoking cessation, with only those passing the posttraining assessment qualifying for participant recruitment.

Experienced research staff will provide supervision and assistance at each recruitment session. Counselor performance will be monitored through regular supervision sessions, participant feedback, and periodic reviews of brief counseling by experienced supervisors. Eligible smokers who decline to participate will be asked to provide their reasons for refusal. Information on the number of approached smokers will be gathered, and smokers’ reasons for declining will be recorded verbatim by the smoking cessation counselors. Weekly group supervision will be conducted to review all active cases.

### Interventions

#### Brief Cessation Advice

All participants will receive 5A/5R cessation advice delivered by well-trained cessation counselors on site. The 5A/5R model consists of 5 steps: ask, advise, assess, assist, and arrange for those who are willing to quit in 30 days and relevance, risks, rewards, roadblocks, and repetition for those who are unwilling to quit in 30 days. The participants will also receive a leaflet and a booklet that contain information and tips to help them quit smoking. The leaflet highlights the absolute risk of death due to smoking, diseases caused by active and passive smoking, explicit pictorial health warnings, the benefits of quitting, and motivational messages. The booklet was designed by the Chinese Center for Disease Control and Prevention and includes topics such as benefits and methods of quitting, relapse prevention strategies, and common myths and facts about smoking.

#### Chatbot-Led Group Support

All participants will join a WeChat group led by a chatbot called the “BNU Cessation Assistant.” The chatbot will greet each participant by name and introduce its functions when the participants join the group. The chatbot will engage the participants in interactive conversations by presenting them with a choice of fixed conversations that will cover topics such as the harms of smoking, benefits and methods of quitting, withdrawal symptoms, cessation medications, and quitting self-efficacy. The chatbot will also provide open-ended conversations using natural language processing techniques and will be accessible at any time. The chatbot will deliver announcements and reminders and prompt the participants to share their stories, difficulties, and achievements with other group members. The participants can also communicate with each other for mutual support and encouragement.

The participants can participate in a smoke-free punch-in activity in the group every day to show their commitment and determination to quit smoking. The punch-in activity asks participants to report their smoking status on that day. If a participant reports being smoke-free, he or she will receive encouragement from the chatbot along with the participant’s number of smoke-free days and ranking among other group members. The aim of the punch-in activity is to motivate the participants to quit smoking by increasing their self-efficacy and providing social support.

#### Counselor-Led Personalized Support

Participants in the intervention group will receive 3-month, counselor-led, personalized support through the WeChat platform. This support consists of 2 main components: individualized counseling and prescheduled messages. First, individualized counseling will be provided through one-on-one sessions with trained counselors proficient in behavior change techniques [31]. The counseling is designed to be both proactive and responsive, with counselors initiating regular check-ins and providing tailored advice via text messages. Participants can also initiate contact with counselors as needed. The counselors will respond promptly to any cessation-related queries within working hours (weekdays from 9 AM to 6 PM). Second, participants will receive 24 prescheduled messages over the 3-month period that match their readiness to quit. These messages are delivered on a tapering schedule: 3 messages per week in the first month, 2 messages per week in the second month, and 1 message per week in the third month. The content of these messages includes education on the harms of smoking, the benefits and methods of quitting, techniques for managing cravings, and information on available cessation services. The messages are designed to initiate conversation, and participants are invited to respond.

